## Abstract

**Background:**

Behavioural lifestyle interventions can be effective at promoting initial weight loss and supporting physical activity and dietary behaviour change, however maintaining improvements in these outcomes is often more difficult to achieve. Extending intervention contact to reinforce learnt behavioural skills has been shown to improve maintenance of behaviour change and weight loss. This trial aims to evaluate the feasibility, acceptability and efficacy of a text message-delivered extended contact intervention to enhance or maintain change in physical activity, dietary behaviour and weight loss among participants who have completed a six month Government-funded, population-based telephone coaching lifestyle program: the Get Healthy Information and Coaching Service (GHS).

**Methods/Design:**

GHS completers will be randomised to the 6-month extended contact intervention (Get Healthy, Stay Healthy, GHSH) or a no contact control group (standard practice following GHS completion). GHSH participants determine the timing and frequency of the text messages (3–13 per fortnight) and content is tailored to their behavioural and weight goals and support preferences. Two telephone tailoring calls are made (baseline, 12-weeks) to facilitate message tailoring. Primary outcomes, anthropometric (body weight and waist circumference via self-report) and behavioural (moderate-vigorous physical activity via self-report and accelerometer, fruit and vegetable intake via self-report), will be assessed at baseline (at GHS completion), 6-months (end of extended contact intervention) and 12-months (6-months post intervention contact). Secondary aims include evaluation of: the feasibility of program delivery; the acceptability for participants; theoretically-guided, potential mediators and moderators of behaviour change; dose-responsiveness; and, costs of program delivery.

**Discussion:**

Findings from this trial will inform the delivery of the GHS in relation to the maintenance of behaviour change and weight loss, and will contribute to the broader science of text message lifestyle interventions delivered in population health settings.

**Trial registration:**

ACTRN12613000949785

## Background

Overweight and obesity, along with insufficient physical activity and unhealthy dietary intake are associated with considerable burden of disease [1,2]. Over 60% of Australian adults are overweight or obese, 62% do not meet national physical activity guidelines and the vast majority do not meet dietary guidelines [2]. These population rates are similar to those in comparable developed countries [3-6]. While multi-sectoral approaches addressing policy, practice and social-environmental factors are needed to tackle obesity at a population level, there remains a need for effective broad-reach, individual-level interventions to support those adults who are currently overweight or obese (estimated nine million Australians) [7] to achieve and maintain moderate weight loss through health behaviour change.

Behavioural lifestyle interventions are effective at promoting initial weight loss [8,9]. However, maintaining improvements in these outcomes is often more difficult to achieve. Evidence indicates an average regain of 0.3 kg per month following the end-of-intervention [10,11], with the average participant regaining approximately 30% to 35% of their weight lost in the first year [12]. Within one [13] to five years [12,14] post intervention, 50% or more of participants are likely to have returned to their baseline weight. The challenge in maintaining weight loss post-intervention has been largely attributed to the failure in maintaining physical activity and dietary behaviour change [14,15].

Evidence from interventions designed to enhance the maintenance of physical activity, diet and weight loss suggests the importance of extended intervention contact after initial intervention [14,16,17]. Extended contact provides the opportunity to reinforce behavioural skills learnt during the initial intervention, support problem solving and provide continued accountability and motivation. A recent meta-analysis of randomised controlled trials (n = 11) of extended contact interventions for weight loss maintenance concluded that they are viable and efficacious [17]. Common features of successful extended contact interventions for weight loss maintenance include: contact from interventionists (rather than peers or non-interventionist contact); and, reinforcement of behavioural skills, particularly support for setting and meeting behavioural goals, problem-solving skills and training in relapse prevention [17]. Previous trials have primarily evaluated extended contact interventions delivered via face-to-face group or individual sessions [18-20], although it has also been shown that face-to-face session attendance decreases as treatment duration approaches one year and as individuals regain weight [14,21]. Some trials have found telephone-delivered extended contact interventions lead to better weight outcomes for participants compared to control groups [21-23]. There is mixed evidence supporting the efficacy of web-based extended contact interventions for weight loss and behaviour change [24], with poor results being attributed to the lack of active and ongoing engagement of participants with the website.

Mobile telephone text messaging may be particularly suited as a delivery modality for extended contact interventions. Text messages can: efficiently deliver tailored repeated contacts from interventionists; be actively “pushed” to participants to maintain contact over long periods of time; prompt behaviours and use of behavioural skills in real time; and, maintain two-way communication with an interventionist using minimal resources. Evidence is rapidly emerging supporting the efficacy of text message-delivered interventions to promote initial weight loss, physical activity and dietary behaviour change [25-30]. Recently, a small (n = 34), pilot trial reported continued weight loss from participants receiving a text message-delivered extended contact weight loss intervention [31]. This area of research holds great promise and requires ongoing investigation.

The Get Healthy Information and Coaching Service® (GHS) is a free, publicly available, telephone-delivered coaching program targeting healthy lifestyle improvements (moderate weight loss, physical activity and dietary behaviours) in adults [32]. The service was launched by the New South Wales Government in Australia in 2009 and since then three additional Australian states have taken it up. Evaluations of the GHS have shown weight loss and behavioural improvements at the end of the 6-month telephone coaching program [33] and evidence of maintenance 6-months after completion of the program for weight loss and some behavioural outcomes in a small sub-sample of participants [34].

This present study will test the feasibility and efficacy of a text message-delivered extended-contact intervention (Get Healthy, Stay Healthy; GHSH) in a randomised controlled trial, among GHS completers. As such, it will inform subsequent improvements to the GHS, in line with the New South Wales Ministry of Health’s commitment to evidence-based service delivery. Findings will also inform the broader field of interventions targeting maintenance of weight loss and multiple health behaviour change, particularly given the ‘real-world’ context of the evaluation and the potentially cost-effective means of intervention delivery. More specifically, in the trial we will assess the: 1) feasibility (intervention delivery and text message receipt tracking) and acceptability (participant satisfaction and engagement) of delivering the GHSH intervention; 2) efficacy of GHSH on changes in moderate-vigorous physical activity, fruit and vegetable consumption, body weight and waist circumference between baseline (at GHS completion) and 6-months (end of extended contact intervention) and 6-months and 12-months (end of maintenance phase); 3) mediators of change due to GHSH intervention (outcome expectancy, satisfaction with perceived outcomes, self-regulation, self-efficacy, social support and perceived environmental opportunity); 4) moderators of change due to GHSH intervention (demographics, health status, changes during initial GHS); 5) dose-responsiveness of GHSH intervention; and, 6) the costs to deliver the GHSH intervention.

## Methods

### Study design

This randomized controlled trial evaluates the GHSH extended contact intervention against a no-contact control group (standard practice following GHS completion). Participants are randomised following completion of the GHS. Data are collected at baseline (after GHS completion), 6-months (end of GHSH) and 12-months (6-months following GHSH completion). This trial commenced recruitment in August 2012 and is expected to be completed in June 2014. This study (main trial and the user testing pilot study) received ethical clearance from the Human Research Ethics Committee at The University of Sydney (Protocol No.: 03-2011/13523).

### Study context

The GHSH extended contact intervention was developed specifically to follow on from the GHS. The GHS is a publicly-available, lifestyle modification program involving ten telephone coaching calls (maximum 30 minute duration) over 6-months from a qualified health coach. The GHS is open to adults (age >18 years) who are at risk of chronic disease because they do not meet healthy eating [35] or physical activity guidelines [36] or they are overweight or obese. The majority of GHS clients are self-referred and contact the GHS via a free-call telephone number after having seen a GHS media advertisement. GHS clients can also be referred by health professionals and general practitioners, which triggers an outbound GHS call to invite them to participate. The GHS coaching calls aim to assist clients to develop skills in goal setting, maintaining motivation, overcoming barriers and making sustainable lifestyle changes [37]. GHS clients are able to tailor the focus of the coaching calls to be on one or all of the following areas: physical activity, healthy food choices and weight loss or maintenance. GHS clients have access to a website offering static educational content and paper-based behavioural and weight tracking tools.

### Participant recruitment

Participants for this study were recruited on a rolling basis from the pool of participants who completed the GHS between August 2012 and February 2013. Eligibility criteria for this study include: living in New South Wales, Australia; no intention of re-enrolling in GHS coaching; not involved in other GHS evaluation sub-studies; and ownership of a mobile telephone. During the recruitment timeframe, all GHS completers were invited to register their interest for the GHSH study by their GHS coach during the final coaching call. Verbal consent to contact was recorded and then GHS coaches emailed client contact details to the researchers. Interested participants were mailed a Participant Information Sheet and Consent Form and then contacted via telephone to establish their eligibility and willingness to consent to participate in the GHSH trial. Verbal consent to participation was audio recorded, and participants returned the signed Consent Form via reply paid post.

### Randomization

Once informed verbal consent was obtained, the participants underwent the GHSH baseline assessment and were randomized to one of the study groups. Participants were stratified based on their change in weight during the GHS (using the median GHS weight loss of 3 kg). Randomization was conducted using a randomization website (http://www.randomization.com), and allocation was conducted by a trained research assistant with no involvement in participant recruitment.

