### Statistical analysis

#### Intervention effects

Data will be analysed using intention-to-treat principles (i.e., participants will be analysed according to their randomly assigned group, regardless of the amount of intervention received). Each primary outcome will be modelled using mixed linear models with random intercepts, the fixed effects of study group, time (6-months/12-months) and a group by time interaction and will adjust for baseline values and potential confounders. Depending on the distribution of the continuous, interval or categorical outcome an appropriate distribution (e.g. normal, log-normal, gamma, negative binomial, binomial) and link (e.g., identity, logit) will be used. These models will assess intervention effects at end-of-intervention (6-months), end-of-maintenance (12-months) as well as differences between end-of-intervention and end-of-maintenance. Potential confounders include baseline demographic, behavioural and health characteristics as well as pre-intervention weight loss and behaviour changes. Those variables associated with the outcome at p < 0.2 will be adjusted as potential confounders. Final models will include all these potential confounders or remove those that do not affect estimates to within ±20% if models show evidence of overfitting. Sensitivity of conclusions to assumptions regarding missing data will be evaluated by comparing results obtained using different techniques of handling missing data (completers analysis, covariate adjustment and multiple imputation).

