### Sample size

The estimated differences between groups in change in primary outcomes (and standard deviations) for this trial are based on the outcomes from the maintenance evaluation of the GHS from 6 to 12 months without ongoing contact (same as control group treatment in the current study) [34] and literature on change in anthropometric and behavioural outcomes during extended contact interventions [17,18,31]. This evidence shows that we can expect small, continued improvements in the GHSH group from baseline to 6 months and declines in the no contact control group. Based on this, the minimum differences of interest in changes between groups from baseline to 6 months for our primary outcomes are: 2 sessions/week of self-reported moderate-vigorous physical activity; 1 serve of fruit per day and 1 serve of vegetables per day; 2 kg body weight; and, 4 cm waist circumference. The sample size requirement was largely determined by self-reported physical activity (sessions/week) as this outcome required the largest number of participants. Allowing for an attrition rate of 20%, the targeted sample size of 106 participants per group (212 in total) is needed to provide a ≥90% power with 5% significance (two-tailed) to detect a between group difference in change of 2 sessions per week of moderate-vigorous physical activity (assuming a standard deviation (SD) of 5.7sessions/week [34] and pre-post correlation (r) of 0.70 [unpublished data]). It is estimated, based on previous evaluations of GHS [34, unpublished data], that this sample size also provides ≥90% power to detect minimum differences of interest in all other primary outcomes including fruit serves/day (assumed SD = 0.9, r = 0.40), vegetable serves/day (assumed SD = 1.5, r = 0.37), weight in kilograms (assumed SD = 16.5, r = 0.97) and waist circumference in centimetres (assumed SD = 13.5, r = 0.80); as well as our additional measures of physical activity (accelerometer-measured moderate-vigorous physical activity minutes/week (assumed difference = 60, SD = 147, r = 0.60) [75]); and dietary behaviours (FFBQ Total Index (assumed difference = 0.20, SD = 0.50, r = 0.70 [76]).

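### The primary model does not force in the factor that stratified randomisation (GHS weight loss, 3 kg), so data-driven covariate rules decide whether it stays

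*Protocol article*

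**What the plan says.** Under Randomization, the protocol article states: "Participants were stratified based on their change in weight during the GHS (using the median GHS weight loss of 3 kg"). It names a randomisation website but no block scheme.

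Under Statistical analysis, Intervention effects, each primary outcome gets a mixed model with random intercepts and "the fixed effects of study group, time (6-months/12-months) and a group by time interaction and will adjust for baseline values and potential confounders". The stratum is not named among these terms. Weight loss before the trial appears one level down: "Potential confounders include baseline demographic, behavioural and health characteristics as well as pre-intervention weight loss and behaviour changes".

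Two rules then govern candidates. The first is a screen: "Those variables associated with the outcome at p < 0.2 will be adjusted as potential confounders". The second is a reduction step: final models keep all the screened variables or "remove those that do not affect estimates to within ±20% if models show evidence of overfitting". Neither rule exempts the stratification factor.

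**The concern.** An analysis should normally reflect the restrictions used in randomisation. When allocation is balanced within strata and the stratum predicts the outcome, the treatment estimate varies less than a model without the stratum assumes. Leaving it out keeps the between-stratum variance in the residual, so the standard error is too wide and the test is conservative.

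A change-in-estimate rule is a poor judge here. It detects confounding, that is, imbalance between groups. Stratification removes the imbalance, so the factor looks dispensable even when it is prognostic. Its value lies in precision and a correct standard error, which the rule does not measure.

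Both rules are also applied outcome by outcome. The design factor could be in the body weight model and absent from the fruit model, depending on the data.

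**Working it through.** **Inputs from the Sample size section.** Target 106 per group; power at least 90%; two-sided 5% level; self-reported activity as the driving outcome, with a difference of 2 sessions a week, SD 5.7 and r = 0.70; attrition 20%.

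**The plan's own figure.** Baseline-adjusted SD = 5.7 × √(1 − 0.70²) = 4.071. Evaluable per group = 2 × [4.071 × (1.960 + 1.282) / 2]² = 87.05, so 88. Then 88 × 1.2 = 105.6, so 106, as stated. With 106 × 0.8 ≈ 85 evaluable per group, SE = 4.071 × √(2/85) = 0.624, the standardised effect is 2 / 0.624 = 3.203, and power = Φ(3.203 − 1.960) = 89.3%. This benchmark adjusts for baseline only; the stratum plays no part in it.

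**Effect of omitting the stratum.** Let R² be the share of baseline-adjusted outcome variance that the stratum explains. The article does not give it, so 2-10% is an assumed range. Assume balance within strata.

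- Reported SE / true SE = 1/√(1 − R²)
- Type I error = 2 × [1 − Φ(1.960/√(1 − R²))]
- Power without the stratum = Φ((3.203 − 1.960)/√(1 − R²))
- Power with it = Φ(3.203/√(1 − R²) − 1.960)

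| R² | SE too wide by | Type I error | Power without | Power with |
|---|---|---|---|---|
| 2% | 1.0% | 4.8% | 89.5% | 89.9% |
| 5% | 2.6% | 4.4% | 89.9% | 90.8% |
| 10% | 5.4% | 3.9% | 90.5% | 92.2% |

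**How often the p<0.2 screen would drop it.** With 170 evaluable and the screen applied to the baseline-adjusted association, the expected t statistic is √(170 × R²/(1 − R²)) against a critical value of 1.287. The chance of being dropped is about Φ(1.287 − expected t).

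- R² 1%: expected t 1.31, dropped in about 49%
- R² 2%: 1.86, about 28%
- R² 5%: 2.99, about 4%
- R² 10%: 4.35, about 0.1%

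**How often the 20% rule would drop it, once invoked.** This was simulated with a single 6-month analysis of covariance: 170 evaluable, two equal strata, permuted blocks of 4 within strata (assumed), 5,000 runs per setting, and ρ the partial correlation of stratum with outcome (R² = ρ²).

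| ρ | Type I error without / with | Power without / with | Estimate moves <20% (true effect 2) |
|---|---|---|---|
| 0.1 | 5.2% / 5.3% | 88.6% / 88.7% | >99.9% |
| 0.2 | 4.5% / 5.0% | 89.4% / 90.1% | >99.9% |
| 0.3 | 4.0% / 5.0% | 90.1% / 91.8% | 99.9% |
| 0.4 | 3.5% / 5.3% | 90.7% / 93.3% | 99.9% |

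Simulation error on the type I figures is about 0.3 points. Without stratified allocation, the same covariate would be deleted in 97%, 92% and 86% of runs at ρ = 0.2, 0.3 and 0.4, so balance by design does raise the chance of deletion. With no true effect, the stratified figure is 84-98% over ρ from 0 to 0.4, because the percentage is then taken of an estimate near zero.

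**The case against.** A reader might infer four stronger things, none of which the article supports.

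- **That the 20% rule discards the stratum as a matter of course.** It applies only if models show evidence of overfitting. Otherwise everything that passes p<0.2 stays, and a stratum explaining 5-10% of variance would pass in about 96% of trials or more. The larger losses above therefore arise almost only if the overfitting step is also triggered, and the article gives no way to judge how likely that is. When the screen alone drops the stratum, it is usually because it matters little: at R² of 1-2% the standard error is 0.5-1% too wide.
- **That planned power falls below its target because of this.** The 89.3% benchmark never included the stratum. Omission forgoes a gain of about 1-2 points over R² of 5-10%; it takes nothing from the plan.
- **That the treatment estimate is biased or false positives increase.** The linear-model estimate is unbiased, and the test errs on the conservative side.
- **That balance is guaranteed.** The article states no blocking. Simple randomisation within strata would give no assured balance, and the standard error without the stratum would then be valid. Attrition of 20% also loosens exact balance.

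It is fair to add that pre-intervention weight loss is listed as a candidate covariate and examined as a moderator, so it is not ignored. Variation of the model between outcomes comes from the selection rules as a whole and is not peculiar to the stratum.

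What survives is that the article itself fixes a rule under which the design factor can be dropped. That is a stated choice, not a detail left to a fuller analysis plan.

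**Conclusion.** The point holds as a modest matter of efficiency and coherence. The factor used to stratify randomisation is not a fixed part of the primary model, and two data-driven rules can remove it, possibly for some outcomes and not others. Once invoked, the 20% rule would almost always remove it, however prognostic it is. The cost of omission at R² of 5-10% is a standard error 2.6-5.4% too wide, type I error of about 4.4-3.9%, and power near 90% where 91-92% was available.

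These figures rest on the assumed R², on blocked allocation within strata, and on a linear model at one time point in place of the full mixed model. The article permits other distributions and links; the statement about bias is made for the linear model only.

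**What to change.** Add one sentence to Intervention effects: the randomisation stratum (GHS weight loss below versus at or above 3 kg, coded as it was at randomisation) is a fixed effect in every primary model and is exempt from the p<0.2 screen and the ±20% removal rule. Stating under Randomization whether allocation was blocked within strata would settle the balance assumption.

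The cost is one degree of freedom per model. No new data are needed: the Data collection section says that change during the GHS comes from the earlier GHS evaluations, and the stratum was needed to randomise. The sample size is unaffected.

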### Get Healthy, Stay Healthy intervention development and pilot testing

The GHSH intervention protocols were informed by a one-month user testing pilot study. Ten pilot participants were recruited during their final GHS coaching call and received an abbreviated user-testing version of the GHSH program (one telephone tailoring call, two weeks of tailored GHSH text messages). After the abbreviated program, participants completed a telephone interview to provide feedback on their experience. The majority of participants were female (8/10) and had lost between 2 to 15 kg body weight during the GHS. Overall, participants were surprised about how supported they felt during the two week text messaging period, with almost all expressing (unprompted) interest in continuing the program for 6-months if given the choice. On average participants opted to receive 10 text messages over two weeks (range 5–13 texts over two weeks). This selected frequency was above the expected rate, and during the follow-up interviews participants expressed that whilst they were happy with the self-selected frequency for the two week study, during a 6-month program they would select a lower frequency. Participants also stated that it was important that they could change the focus of their behavioural goals over time *“so it doesn’t get boring and repetitive”*. One participant did not like the tone of the language used in the text messages and found the phrasing *“patronising”*. The findings of this pilot study led to the following changes in the GHSH intervention protocol: participants can request changes to the text message frequency at any stage of the 6-month program; participants are prompted every 6-weeks to update their behavioural and weight goals; and, the language of the GHSH texts was revised to remove any overly directive terms.

